## Methods/design

### Study design and mentor-mentee matching

The study is a multi-site collaborative trial conducted at Eating Disorders Victoria (EDV), The Melbourne Clinic (TMC),  and the Body Image and Eating Disorders Treatment and Recovery Service (BETRS) at the Austin Hospital (inpatient unit) and St Vincent’s Hospital (intensive day patient program), all in Melbourne, Victoria, Australia. Up to 30 mentees with an eating disorder (anorexia nervosa, bulimia nervosa, binge eating disorder or eating disorder not otherwise specified, according to the Diagnostic and Statistical Manual of Mental Disorders 5) will be matched with up to 30 mentors with a past history of an eating disorder. Participation will involve a longitudinal study assessing the efficacy of a peer mentor program for individuals with eating disorders. All mentees and mentors will be over the age of 18 years.

As this is a pilot proof-of-concept feasibility study, a randomised controlled trial will not be undertaken, but the program will be evaluated with a within-group design. Participation will involve a series of 13 mentoring sessions of up to 3 h each (ideally, every 2 weeks) over 6 months, following the mentee’s discharge from the BETRS/TMC inpatient unit or transition to/from the BETRS/TMC intensive eating disorders day program. The peer mentoring program will be delivered in a variety of community settings, i.e. local shopping centres, parks and cafes. Mentees and mentors will not be permitted to meet in either person’s home.

Mentors will be employed as ‘casual’ employees of EDV (see Additional file 1: Appendix A) and will be reimbursed for any reasonable expenses incurred during mentoring sessions as part of their employment, i.e. lunch for mentee and mentor, public transport fares for mentee and mentor practicing independent use of public transport, etc. Mentors and mentees will not receive any payment or reimbursement for this research.

Mentees and mentors will be paired on the basis of information provided by both parties. Mentees will be asked to provide a short statement about their values and interests and information about their preferences for working with a mentor of a same/different age, gender, eating disorder history and geographic area. Mentors will be asked to provide a short personal statement about their values and work style to facilitate effective matching. Each pair will be matched with a focus on the best match for the mentee by EDV and BETRS/TMC staff. If a mentor chooses to discontinue their employment on this project, EDV will re-match the mentee with another mentor as soon as practicable and they will continue to work towards the goals identified in their Wellness Plan (see Additional file 1: Appendix B). If a mentee chooses to discontinue with the program, then their mentor will return to the pool of mentors available to be matched with another referral.

### Recruitment procedure

Mentees will be recruited from the partner hospital inpatient unit (the Austin Hospital) and intensive day program (St Vincent’s Hospital), collectively known as the BETRS; and TMC. A member of the research team at BETRS/TMC will identify potential mentees and approach them with the study information form. Mentors will be recruited by EDV according to EDV policy and procedures. Mentors will be employed explicitly for this role and will be invited to participate in the research component of the program by one of the research staff. Participation will be voluntary. The suitability of mentors will be assessed during the interview process for their employment and by one of the researchers when approached for participation in the research component of the project. A minimum of 2 years in recovery will be required as indicated by the clinical measures that will be used to assess current or recovered eating disorder stages (demographics and medical history form).

Written informed consent will be obtained from all participants (mentees and mentors) prior to the commencement of the peer mentor program, by a member of the research team.

#### Eligibility criteria

Inclusion criteria for *mentees* include:Transitioning out of the BETRS inpatient program at the Austin Hospital or TMC, or transition in/out of the BETRS/TMC outpatient/day patient programCurrent diagnosis of an eating disorder (anorexia nervosa, bulimia nervosa, binge eating disorder or eating disorder not otherwise specified) according to the Diagnostic and Statistical Manual of Mental Disorders (DSM-5)Currently actively receiving treatment for their eating disorder for the duration of the program. (See Wellness Plan in Additional file 1: Appendix B). At a minimum, mentees must be receiving care from a GP and a psychologist.

Inclusion criteria for *mentors* include:Recovery from an eating disorder for a minimum of 2 years as indicated on the demographics and medical history form, in combination with the Eating Disorder Examination Questionnaire (EDE-Q). The wellness criteria are evidenced by self-reported absence of eating disorder symptoms (indexed by the EDE-Q), being weight-restored, not receiving treatment for eating disorders symptoms and use of a personal Wellness Plan/self-care activities to maintain their recovery. The Wellness Plan also outlines signs that indicate a mentor is struggling and how to best support them during these times.Successful recruitment as a staff member at EDV, including referee checks and agreement code of conduct

Exclusion criteria for mentors and mentees include anyone who is at serious risk of harm to oneself or another, as determined by the clinical team, for example, individuals at high risk of suicide.

### Mentor training

Mentors will attend a 3-day training and induction program prior to the program rollout to ensure that mentors are prepared in their role. EDV staff and external trainers deliver different elements of the training dependent on their experience. As the mentors are EDV staff, the training starts with inducting them as employees and going through the procedures and policies outlined for all EDV staff members.

An overview of the Intentional Peer Support (IPS) model is given to all mentors as a framework to base all interactions. This model states that peer support is intentional, in that we come to the relationship with a specific purpose in mind—with the program, this is maintaining recovery. The four core elements of IPS are connection—between the mentor and mentee, holding a worldview and understanding how we have come to know what we know and mutuality—learning and growing together and moving towards identified goals (recorded in the mentee’s Wellness Plans) [27].

Training also covers off the challenging situations mentors might be faced with when supporting their mentee. Information about the program’s aims and objectives are made clear so the mentors know what they are working towards. As there is a high possibility of self-harm and thoughts of suicide, all mentors complete an internationally recognised safeTALK suicide alertness workshop which covers hands-on skills to be able to respond to someone who has the thoughts of suicide [28]. The EDV psychologists also facilitate role-plays with mentors which raise common issues and are discussed.

### Mentoring activities

The program will involve 13 mentoring sessions of up to 3 h each, ideally completed every 2 weeks, over 6 months. Mentoring activities will include peer support activities such as providing information, emotional support and sharing of their own recovery experience. Mentoring activities are guided by each individualised mentee’s Wellness Plan (see Additional file 1: Appendix B), formulated during the first mentoring session. This focuses on the mentee’s short-term goals in the following domains: living circumstances and skills, health, self-care, social relationships and connectedness, creative interests and hobbies, work/career and education, identity and sense of self, and community roles and responsibilities. The Wellness Plan also outlines the mentee’s current recovery strategies (e.g. thoughts, feelings, behaviours, characteristics, personal qualities, interests, activities and relationships) that support the mentee to remain healthy as well as articulate warning signs that indicate additional professional support or treatment should be sought (e.g. symptoms, thoughts, images, feelings, mood and behaviours). Mentors will also complete their own amended Wellness Plan which allows them to document self-care strategies and identify potential risks to ensure that program staff can support and ensure the mentor role is not detrimental to their continued health and wellbeing.

Sessions 2–12 of the mentoring activities will focus on supporting the mentee to work toward their identified goals through community-based activities such as supermarket shopping, self-care activities, reconnecting with community or navigating social interactions involving food. Mentors will share aspects of their own recovery stories to promote hope and provide an empathic response to the challenges associated with recovery.

Session 13 of the mentoring activities will focus on completion of a Program Summary outlining the mentee’s progress and achievements (see Additional file 1: Appendix D). This will include a future-focused component encouraging the mentee to identify strategies and alternative supports to draw upon after the pilot program has concluded, in order to sustain their progress.

Mentors will complete an online questionnaire at the conclusion of each mentoring session to document progress and monitor safety considerations (see Additional file 1: Appendix C). This will be reviewed by the EDV project coordinator and allows timely follow-up with any mentee or mentor needing individual support.

### Facilitated group sessions

Throughout the program, mentees will also participate in three group sessions with other mentees, facilitated by an expert clinician in eating disorder treatment. These sessions enable mentees to provide feedback on their experience of the program and increase a sense of community among mentees. Mentors will also attend three group sessions facilitated by an eating disorder clinician in order to debrief about their experiences working in the program and to increase a sense of community among mentors.

All group sessions will take place at the EDV office and will be facilitated by two professional staff, including one with psychological qualifications. The group sessions will be offered three times to mentees during the program. Group sessions for mentors will be provided three times during the program and all mentors will be expected to attend.

### Program evaluation

Informed consent will be sought by one of the research staff from all mentees and mentors to take part in the evaluation of the program, which includes quantitative and qualitative measures. Quantitative data will be collected in a re-identifiable form at baseline (beginning of the program), at 3-month (mid-program) and 6-month (end-of-program) time points, and at 12-month follow-up for both mentees and mentors (see Fig. 1). Qualitative assessments will involve online reflection exercises completed at baseline, mid-program and end-of-program time points, and a qualitative interview undertaken upon completion of the program for both mentees and mentors. In addition, attrition will be tracked by the researchers through records of sessions that the mentors keep.

**Fig. 1 Fig1:**
[figure not shown]
Study procedures, mentee and mentors

#### Quantitative assessments

The following quantitative measures will be collected at each time point to determine the efficacy of the peer mentor program for reducing eating disorder symptoms and quality of life:Clinical demographic and medical history questionnaire: Basic demographic information and a brief medical history will be collected at baseline. At other time points, changes to demographic information and medical history (e.g. new hospital admissions) will be recorded.Eating Disorders Examination Questionnaire (EDE-Q) [29]: The EDE-Q is a 28-item self-report measure of psychological constructs shown to be clinically relevant in individuals with eating disorders. This measure will be used to gather information about eating disorder symptomatology.Depression Anxiety Stress Scale (DASS-21) [30]: The DASS is a 21-item self-report instrument designed to measure the three related negative emotional states of depression, anxiety and tension/stress. Common comorbidities such as depression and anxiety [31] can impact outcomes as well as engagement and adherence and are important targets for intervention as well as being potential adverse outcomes which require monitoring and appropriate action if they reach concerning levels of risk.Brief Disability Questionnaire (BDQ) [32]: The BDQ is a self-report measure of disability in everyday activities and yields two main subscales: physical disability and mental health disability.Assessment of Quality of Life (AQoL) [33]: The AQoL is a self-report instrument that measures health-related quality of life.Feedback questionnaire (not at baseline): General feedback on the program will be sought.

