##### Qualitative interviews and feasibility

Given the limitations of the existing literature, the explorative nature and the qualitative research methodology of the current investigation, a broad semi-structured interview schedule will be used on completion of the program. This will be revised iteratively throughout the study to enable exploration of new themes raised by participants (mentors and mentees) and enable detailed exploration of the most important and relevant themes associated with participating in this program. The qualitative interviews will also cover areas A–C (see Additional file 1: Appendix F). The number of mentoring sessions completed and the participants’ capability to complete the mentoring sessions will also be assessed through the qualitative interviews.

Feasibility of the program will be guided by the CONSORT statement regarding assessing feasibility of trials [36]. Specifically, feasibility will be measured in terms of achieving sufficient numbers of participants signing up, participating and being retained in the program through the qualitative interview and records kept by mentors regarding program participation. The study will be deemed feasible if 80% of participants are able to complete the program and the target sample size is achieved within 2 years. Feasibility will also be measured in terms of tolerance and acceptance of the intervention, that the intervention can be delivered as per the protocol and identifying any adverse events related to the study through the qualitative interview and the participant feedback questionnaires. Any serious adverse events will result in the intervention not continuing to an RCT.

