## Statistical methods

### Sample size estimation and justification

Thirty mentors and a minimum of 30 mentees will be recruited. This minimum sample size of 60 participants will enable differences to be identified between time points in a pilot evaluation (i.e. 28 participants per group will enable the identification of a moderate effect size with power of 0.8 and alpha of 0.05 for a within-group analysis between baseline and the primary endpoint). Sample size has been determined using the qualitative principle of data saturation, which provides an estimate of sample size based upon the comprehensiveness of the data set to identify all of the issues affecting the population under study. As Fusch and Ness [37] highlight, data saturation is the point when (a) no new insights related to the research aims and objectives are gained from additional interviews or through further analysis and (b) there is sufficient information gathered for the study to be replicated. The proposed participant numbers of 60 or more participants (30 per group) is deemed be sufficient to capture the variance in information that occurs within each participant group. Guest and colleagues [38] argue that data saturation occurs after as few as six interviews, with all information (themes) fully elucidated after 12 interviews. Our prior clinical-based qualitative research [39–41] indicates that this varies considerably based on the population under study but typically occurs after 7 and 14 interviews. Given the variability in the present sample by age, gender and anything else, our planned sample will be sufficient to gather powerful information on our study aims and objectives.

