### Statistical methods

Quantitative analyses will include within-group analyses of variance (ANOVAs) and non-parametric assessments between time points, for mentees and mentors separately. Multiple imputation procedures that utilise the expectation-maximisation (EM) algorithm with bootstrap estimates of standard errors will be used for missing data. Using the six-stage approach described by Braun and Clarke [35], thematic analysis will be undertaken to identify key themes in the qualitative data.

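### Depression and anxiety, measured by the DASS-21, are named as potential adverse outcomes, but the DASS-21 is not among the stated adverse-event sources and the named analyses are group-level only

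*Protocol article*

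**What the plan says.** Protocol article, Quantitative assessments: the measures share one declared purpose, "The following quantitative measures will be collected at each time point to determine the efficacy of the peer mentor program". Within that list, the DASS-21 entry gives depression and anxiety a second role besides that of intervention target. It describes them as "being potential adverse outcomes which require monitoring and appropriate action if they reach concerning levels of risk".

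Program evaluation: the measures are taken at baseline, then "at 3-month (mid-program) and 6-month (end-of-program) time points, and at 12-month follow-up for both mentees and mentors".

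Qualitative interviews and feasibility: part of feasibility is "identifying any adverse events related to the study through the qualitative interview and the participant feedback questionnaires". The same section adds a consequence: "Any serious adverse events will result in the intervention not continuing to an RCT". The interview takes place once, when the program ends. The feedback questionnaire is given at the time points after baseline and asks for general feedback.

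Statistical methods: "Quantitative analyses will include within-group analyses of variance (ANOVAs) and non-parametric assessments between time points, for mentees and mentors separately".

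Two other sections make harm part of the conclusions. Study AIMS counts the absence of concerning study-related adverse events as an element of feasibility, and the Discussion undertakes to assess adverse effects in both mentees and mentors.

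**The concern.** If depression and anxiety may be adverse outcomes, the instrument that measures them would be expected to inform the harm assessment. As written, its scores go to an efficacy analysis and the harm assessment draws on other material.

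The efficacy analysis does not fill the gap. ANOVA and rank-based comparisons between time points both describe change in the group as a whole. Mentees must be in active treatment throughout (Eligibility criteria), so some improvement in the group is plausible with or without mentoring, and there is no control group. A few participants who worsen can be outweighed by the rest.

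At stake is the harm part of the feasibility conclusion. The study could complete its stated adverse-event assessment without using symptom scores it has already collected at four time points, the last of them six months after the interview.

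**Working it through.** **The plan's own figure.** The only relevant calculation in the article is the statement that "28 participants per group will enable the identification of a moderate effect size with power of 0.8 and alpha of 0.05". It does not say what counts as moderate. Taking f = 0.25, within-person correlation 0.5 and three time points, the noncentrality is 0.25² × 28 × 3 / (1 − 0.5) = 10.5 on 2 and 54 degrees of freedom. Power is then 0.812, and 28 is the smallest n that reaches 0.8. The figure is reproducible, but it concerns detecting group change, and the present point does not depend on it.

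**The sections side by side.**
- Quantitative assessments: depression and anxiety are possible harms that need monitoring, and the DASS-21 measures them.
- Qualitative interviews and feasibility: adverse events come from the interview and the feedback questionnaires.
- Mentoring activities: mentors complete a survey after every session, which the project coordinator reviews. It is not linked to the DASS-21.
- Risk management and safety: there are support contacts, and guidelines for self-reported increases in eating disorder symptoms or risk. These are not linked to the DASS-21 either.

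So no stated route carries a DASS-21 score into the feasibility judgement on harm.

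**Can a group comparison miss a worsening minority?** The documents give no DASS-21 figures, so every input here is an assumption except n = 30, which comes from the sample size section. Suppose k mentees have mean change +1 SD (worse), the rest have mean change −0.5 SD, and individual change varies around these means with SD 0.8. The test is a two-sided paired t-test at 0.05, with critical value 2.045 on 29 degrees of freedom.
- k = 5: mean change = (5 × 1 − 25 × 0.5)/30 = −0.25. Between-subgroup variance = (5 × 1.25² + 25 × 0.25²)/30 = 0.3125, so total SD = √(0.64 + 0.3125) = 0.976. The typical t is −0.25/(0.976/√30) = −1.40. In 40,000 simulated trials, significant worsening appears in under 0.1% and significant improvement in about 23%.
- k = 3: mean change = (3 × 1 − 27 × 0.5)/30 = −0.35. Significant improvement appears in about 52% of trials and worsening in essentially none.
- k = 5, others improving by only 0.3 SD: worsening is flagged in under 0.3%.
- k = 5, others unchanged: worsening is flagged in about 14%. The masking therefore depends on the others improving.

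A Wilcoxon signed-rank test behaves like the t-test in the first two cases: no trials show worsening, and improvement appears in about 27% and 56%.

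A second set of assumptions gives the same picture. Each of 30 mentees worsens by 0.8 with probability 10%, 20% or 30%, the others improve by 0.8, and the residual SD is 0.6. Improvement is significant in 98%, 80% and 43% of trials. If the others improve by only 0.5, the figures are 77%, 37% and 11%. Worsening is significant in at most 0.3% throughout.

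**What would a count of worsened participants show?** In the first scenario, the expected number whose observed change exceeds a cut c (in SD) is 5·Φ((1 − c)/0.8) + 25·Φ((−0.5 − c)/0.8). The comparison is a homogeneous group with no harmed subgroup but the same mean and total SD: 30·Φ((−0.25 − c)/0.976).

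| Cut c | From the 5 | From the 25 | Total | Homogeneous group |
|---|---|---|---|---|
| 0 | 4.5 | 6.6 | 11.1 | 12.0 |
| 0.5 | 3.7 | 2.6 | 6.3 | 6.6 |
| 1 | 2.5 | 0.8 | 3.3 | 3.0 |

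The totals are nearly the same with and without a harmed subgroup. A count records how many participants were observed to worsen. It does not recover the five who truly did.

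**Precision.** Exact 95% intervals with 30 participants are 0% to 11.6% for 0/30, 2.1% to 26.5% for 3/30, and 7.7% to 38.6% for 6/30.

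**The case against.** The strongest reply is that this is a journal article. Its analysis section is one sentence stating what the analyses will include, which is not an exhaustive list, and tables of individual worsening are commonly left to a statistical analysis plan. That stands: the absence of such a table would not be a finding by itself. It does not remove the disagreement between two statements that are in the text.

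A second reply is that participants are watched individually, through the session survey, the support contacts, the guidelines for increased symptoms or risk, and the recording of new hospital admissions. This also stands. A reader might infer that the plan hides mentees who deteriorate, or that nobody would notice them. The documents do not support that. These routes concern the care of individuals as the program runs, and the session survey is more frequent than the DASS-21. What is missing is a stated link from DASS-21 scores to any of them or to the feasibility conclusion.

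Third, the feasibility section names two sources without excluding others, and it is depression and anxiety, rather than DASS-21 scores, that are called adverse outcomes. Both remarks are correct. They make this a matter of reconciling text and not of correcting an analysis error.

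Finally, a count is noisy and the study is uncontrolled. The table above confirms that this limits what the count can say.

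**Conclusion.** The point holds as a mismatch within the article. Conditions described as potential adverse outcomes are measured at every time point, yet their measure is not named among the sources for the adverse-event part of feasibility. The analyses that are named describe the group. Under the assumed inputs, those analyses flag worsening in under 0.3% of trials when the remaining mentees improve by 0.3 to 0.5 SD, and in about 14% when they do not change. These percentages show that masking is possible; they do not predict this trial.

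Three stronger readings go too far. One is that a direct count would have reported exactly the five worsening mentees of the illustration; scatter in individual change rules that out. Another is that an improved DASS-21 mean would be taken as evidence of safety; nothing in the documents says so. The third is that a DASS-21 worsening would trigger the rule against continuing to an RCT; that rule concerns serious adverse events, and no DASS-21 change is defined as one.

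The point is not confined to mentees. Mentors complete the same instrument, and the Discussion promises an assessment of adverse effects in both groups. It is a modest point, worth making because the data are already collected.

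**What to change.** Reconcile the DASS-21 entry under Quantitative assessments with the adverse-event sentence under Qualitative interviews and feasibility, by listing the DASS-21 among the sources considered for the adverse-event part of feasibility.

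Under Statistical methods, keep the group-level analysis and add a descriptive summary. For each DASS-21 subscale, and for mentees and mentors separately, give the number and proportion whose observed score has worsened from baseline by a pre-specified criterion at 3, 6 and 12 months, with exact 95% confidence intervals and the number observed. Use observed rather than imputed scores, because the aim is to report what happened to individuals. The trial team should set the criterion before looking at the data. It is a reporting criterion, and no clinical action threshold is proposed here.

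The cost is about one sentence in each of the two sections and one table, with no new data collection. The downside is that some worsening will reflect measurement error or the natural course of illness. The table should therefore state that it neither isolates a harmed subgroup nor attributes harm to the program.
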